### Sample size

No formal sample size calculation was performed for this feasibility study. However, a minimum sample size for a pilot study to evaluate the feasibility of conducting a full-scale trial is suggested to be 50 per study [18, 19]. A total of 78 patients (26 per arm) were deemed an appropriate sample size for this trial to estimate the recruitment and retention rates and explore the acceptability of the intervention.

### Randomization and allocation

Upon completion of the 12-week post-operation assessments, TKA participants will be randomized into either the intervention or the usual care group. Permuted blocks using a computer-generated random number schedule will be used to determine the randomization order. Group assignment will be concealed in sealed sequentially numbered opaque envelopes and administered by a research assistant at The Hong Kong Polytechnic University not involved in the study. In addition, various methods will be employed to keep participant data confidential and secure including using password-protected files, limiting access to only those on the study team who require identifiable data, and using de-identified data when possible.

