**Methods:**

A single-blinded 2-arm pilot randomized controlled trial will recruit 52 community-dwelling post-TKA patients (aged > 60 years) in Hong Kong. In addition, 26 untreated asymptomatic controls will be recruited for comparison purposes. The TKA patients will be randomized into either a 12-week multimodal Tai Chi rehabilitation group or a postoperative usual care group (26 each). Participants will perform the outcome assessments at baseline, 6, 12, 24, and 52 weeks after TKA, while asymptomatic controls will have the same assessments at baseline, 12, and 52 weeks after baseline. The rate of recruitment, retention, and attrition, as well as adherence to the intervention, will be measured and used to determine the feasibility of the study and whether a full-scale effectiveness trial is warranted. Further, qualitative interviews will be conducted to explore the acceptability and possible barriers to the implementation of the intervention. Primary and secondary outcomes including both patient-reported surveys and performance-based tests will be compared within and between groups.

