## Methods

### Study design

This is a single-blinded 2-arm RCT. TKA participants will be randomized to either a 12-week community-based rehabilitation program starting at 12 weeks after TKA, or usual postoperative care without outpatient physiotherapy. A third group of asymptomatic controls will be recruited to provide comparisons at various time points (Fig. 1). A third group of asymptomatic controls will be recruited to investigate whether the postoperative rehabilitation program can restore balance and mobility of TKA patients to the levels found in asymptomatic individuals (Fig. 1). All post-TKA participants will undergo five clinical assessments: 1 week before TKA, and at 6, 12, 24, and 52 weeks after TKA. Two orthopedic surgeons will use a standard parapatellar approach. Two common prosthesis designs (posterior stabilized and medial pivot) will be used in TKA surgery. Previous research has reported no significant differences in self-reported and physical performance outcomes between these prostheses 12 months after TKA [16]. In addition, the untreated asymptomatic controls will be assessed at baseline, and 12 and 52 weeks from baseline. This study protocol has been approved by the Human Research Ethics Committees at The Hong Kong Polytechnic University (HSEARS20171225001) and the Institutional Review Boards of two hospitals (UW 18-452) and has been prospectively registered on clinicaltrials.gov (identifier number: NCT03615638). The protocol has been developed in accordance with Good Clinical Practice, Standard Protocol Items: Recommendation for Interventional Trials (SPIRIT) (see Additional file 1 SPIRIT 2013 checklist). The Human Research Ethics Committees review all study activities annually including ethical conduct, regulatory compliance, and recruitment and retention and can initiate an independent study audit at any time. The investigator team meets biweekly to discuss enrolment targets and treatment fidelity. The study coordinator is responsible for ensuring that data is complete and monitoring study progress including sufficient recruitment and retention. Adverse events across conditions will be reviewed annually; issues with intervention delivery and other unintended consequences of either intervention are discussed during regular supervision meetings. Significant protocol modifications will be approved by relevant Institutional Review Boards and will be reported to relevant parties (e.g., ClinicalTrials.gov) in a timely manner. All participants have the option of discontinuing their participation in the study at any time, and this is indicated in the consent forms. Adverse events will be reported immediately to the principal investigator, tracked, and responded to according to regulatory guidelines. There are no criteria for the modification of the study interventions. As harm from this type of study is rare, there are no provisions in place for ancillary, post-trial, or compensation for study-related harms.

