### Blinding

All assessments of TKA patients will be conducted by blinded physiotherapists/trained research personnel at one of the two participating hospitals. However, participants and Tai Chi instructor will not be blinded.

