#### Usual postoperative care group (Fig. 1)

Participants in the usual care arm will receive standardized usual inpatient postoperative care provided by the two participating hospitals and a total knee replacement pamphlet. The pamphlet contains information about early-stage postoperative exercises including lower limb stretching and mobilization exercises. In addition, some patients may be referred to outpatient physiotherapy services at the discretion of the physiotherapy or orthopedic team upon discharge or medical follow-ups. Upon the completion of all 5 assessments, participants will be given a maximum compensation of HK$250 supermarket coupons*.*

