## Statistical analysis

The data regarding the feasibility, acceptability, adverse events, intervention adherence, missing data rates and data completion rates will be summarized using descriptive statistics. The experience and perception of participants toward the RCT solicited from semi-structured interviews will be analyzed by framework analysis [39, 40].

To determine the feasibility of studying the proposed outcomes in a definitive trial, inferential analysis will be conducted at 95% confidence intervals, and the significance level will be set at 0.05. The effect size of each intervention outcome will also be estimated. Descriptive statistics will be used to summarize patient demographic data. Baseline demographic and clinical variables (such as BMI, medication, number of comorbidities) in the three groups will be compared using analyses of variance (ANOVAs) and Kruskal-Wallis tests for parametric and nonparametric data, respectively. Any baseline variables that show significant between-group differences will be used as covariates in subsequent between-group analyses of outcome measures. Separate two-way repeated measures analyses of covariate (ANCOVA) or ANOVA will be used to evaluate within- and between-group changes in various outcome measures at several follow-up time points (i.e., 6, 12, 24, and 52 weeks after TKA for TKA patients, and 12 and 24 weeks after baseline for asymptomatic controls) in the three groups. Statistical analyses will be conducted using SPSS version 21.0 (IBM Corporation, NY, USA). Following the intention-to-treat principle, between-group differences in primary and secondary continuous outcomes in all randomized participants at different time points will be analyzed. Per-protocol analysis will also be reported for all planned outcomes in participants who strictly followed the protocol.

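### Two hospitals, no stratification by hospital named, and adjustment only after a significant baseline test: a pre-specified hospital term is a cheap gain in precision

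*Protocol article*

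**What the plan says.** - **Sites.** The Recruitment section draws TKA patients from the clinics of two hospitals. The Abstract gives 52 patients, 26 per arm. The share from each hospital is not stated.
- **Allocation.** The Randomization and allocation section states: "Permuted blocks using a computer-generated random number schedule will be used to determine the randomization order". Envelopes are "administered by a research assistant at The Hong Kong Polytechnic University not involved in the study". No stratification factor is named. Neither is one ruled out.
- **Timing.** "Upon completion of the 12-week post-operation assessments, TKA participants will be randomized into either the intervention or the usual care group". Surgery and inpatient care are therefore complete before allocation.
- **Care by team.** In the usual care section, "some patients may be referred to outpatient physiotherapy services at the discretion of the physiotherapy or orthopedic team upon discharge or medical follow-ups". The same section describes inpatient care as standardized across the two hospitals.
- **Analysis.** In the Statistical analysis section, baseline variables in the three groups are "compared using analyses of variance (ANOVAs) and Kruskal-Wallis tests for parametric and nonparametric data". Those with a significant between-group difference become covariates. Hospital is not among the examples given, but the list is open.

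**The concern.** Hospital is the obvious grouping factor in a two-site trial. Discretionary physiotherapy referral is one concrete route by which care could differ between the sites, including after randomisation. With 26 patients per arm, simple chance can put noticeably more of one hospital's patients into one arm. If hospital is related to an outcome, part of the estimated difference between arms is then a difference between hospitals.

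The stated covariate rule protects poorly against this. It brings hospital into the model only when the imbalance is large enough to be significant, and a moderate imbalance passes through. At stake are the exploratory effect sizes and, to a small degree, the KOOS standard deviation meant to inform the definitive trial's sample size.

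**Working it through.** The protocol makes no formal sample size or power calculation, so there is no figure of its own to reproduce.

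**Inputs.** From the protocol: 52 patients, 26 per arm, two hospitals, significance level 0.05. Assumed: allocation not stratified by hospital; a hospital split from 50:50 to about 80:20; a hospital difference *d* in the analysed outcome of 0.5 SD (range 0.25 to 0.8); no losses to follow-up.

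**Step 1: how often the arms differ in hospital mix.** Let *K* of the 52 patients come from hospital A. The number *x* of these in one arm of 26 is hypergeometric(52, *K*, 26). The gap in hospital share is |*x* − (*K* − *x*)| / 26. A two-arm, uncorrected chi-square test at 0.05 stands in for the baseline test.

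| Hospital split | Gap ≥ 15 points | Gap ≥ 20 points | Smallest gap flagged | Chance of being flagged |
|---|---|---|---|---|
| 26:26 | 40.6% | 16.5% | 31 points | 5.1% |
| 31:21 | 25.8% | 8.9% | 27 points | 8.9% |
| 36:16 (about 70:30) | 36.8% | 13.2% | 31 points | 3.4% |
| 42:10 (about 80:20) | 29.1% | 7.5% | 23 points | 7.5% |

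Gaps come in steps of 2/26, so the figures do not move smoothly with the split. At 26:26, the first gap above 20 points is 16 v 10 (6/26 = 23 points). At 31:21 and 42:10, every gap of 20 points or more would be flagged, so the unflagged imbalance there lies between 15 points and the threshold. A gap of at least 15 points that escapes the test has probability 40.6 − 5.1 = 35.5% at 26:26, and 25.8 − 8.9 = 16.9% at 31:21.

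Simulating permuted blocks of 4 or 6 (block sizes assumed), with the hospital counts left to chance, puts a gap of 20 points or more at 12.5–12.6% for a 50:50 mix and 9.3–11.0% for 70:30.

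**Step 2: the flagging threshold at 26:26.** For 17 v 9, chi-square = 52 × (17² − 9²)² / 26⁴ = 52 × 208² / 456,976 = 4.92, p = 0.027. For 16 v 10, chi-square = 52 × (16² − 10²)² / 26⁴ = 52 × 156² / 456,976 = 2.77, below the 3.84 needed. The 23-point gap is not flagged.

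**Step 3: effect on the estimate.** Shift = gap × *d*. With a 23-point gap: 0.23 × 0.5 = 0.12 SD (0.06 at *d* = 0.25; 0.18 at *d* = 0.8). The standard error of the arm difference is √(2/26) = 0.28 SD, so the central shift is 0.12/0.28, a little over 40% of one standard error.

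**Step 4: precision.** Leaving hospital out adds *p*(1 − *p*)*d*² to the residual variance, where *p* is the hospital share. The interval narrows on adjustment by 1 − 1/√(1 + *p*(1 − *p*)*d*²). At *p* = 0.5 and *d* = 0.5 this is 1 − 1/√1.0625 = 3.0% (0.8% at *d* = 0.25; 7.2% at *d* = 0.8).

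**Step 5: what stratifying would do.** In 20,000 simulated trials per setting, stratified blocks cut the SD of the gap from about 13–14 points to about 3. The largest gap seen was about 10 points.

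**The case against.** The strongest reply is that the allocation half rests on silence. A journal article may leave stratification and block size to the full protocol. That stands: the text does not show a single list that ignores hospital, and Step 1 is conditional on it. The analysis half does not rest on silence, because the covariate rule is stated. If blocks were stratified, hospital would still belong in the model, and the rule does not put it there.

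Second, a constant difference between hospitals cancels in within-person change, and the plan analyses change over repeated visits. This also stands. For change from the week-12 assessment, *d* must be a hospital difference in later change, so the effect is smaller than in Step 3.

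Third, randomisation without stratification is unbiased, and the confidence interval already allows for chance imbalance. The trial is a feasibility study not powered for efficacy. Both points are correct and limit the weight of the concern.

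A reader might infer more than the documents support:

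- **Surgeon, implant or assessor coincide with hospital.** Two surgeons and two prosthesis designs are used, but neither is tied to a hospital. The Blinding section says only "All assessments of TKA patients will be conducted by blinded physiotherapists/trained research personnel at one of the two participating hospitals", not that patients are tested where they had surgery.
- **The named tests cannot handle hospital.** They can for two levels: Kruskal-Wallis on the 17 v 9 split gives H = 4.92 × 51/52 = 4.83, p = 0.028.
- **The sentence on prostheses is the plan's reason for ignoring hospital.** It concerns prosthesis design only and is not offered for that purpose.

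**Conclusion.** The point holds as a modest precision improvement. The protocol names no stratification by hospital, and its covariate rule would usually leave a moderate hospital imbalance unadjusted. The size rests on two assumptions that the documents do not settle: that allocation is unstratified, and that the hospitals differ by about 0.5 SD in the analysed outcome. Within the range considered, neither the shift from a 23-point gap nor the gain in interval width would by itself change a reading of the trial. Any hospital variance left in the KOOS standard deviation would make the later sample size slightly too large, not too small. Recruitment, retention and acceptability results do not depend on this.

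**What to change.** In the Statistical analysis section, include hospital as a pre-specified fixed term in every intervention-versus-usual-care model, whatever any baseline test shows. This serves patients already randomised as well as any to come, and costs one degree of freedom.

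In the Randomization and allocation section, state whether blocks are stratified by hospital. If they are not, stratify for any patient still to be randomised, and in the definitive trial: two sequences and two envelope sets, held by the same independent research assistant. Few patients may be left to benefit, since the Trial status section has recruitment closing on 1 November 2020. Incomplete blocks in two strata may leave the arms slightly unequal, for example 25 v 27. No extra patients, visits or staff are needed.

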### Blinding

All assessments of TKA patients will be conducted by blinded physiotherapists/trained research personnel at one of the two participating hospitals. However, participants and Tai Chi instructor will not be blinded.

### Instructor

The researchers completed a Tai Chi certificate workshop for exercise leaders in Hong Kong provided by [name], who had originally developed the 12 movements of Sun-style Tai Chi exercise for arthritis. During the workshop, the intensity and forms of the 12 Tai Chi movements of exercise leaders were closely monitored to ensure that each movement would be applied correctly and safety to patients with arthritis. An illustrated training manual and reference guide along with the a standardized home-practice DVD (ISBN 978–0–9,803,573-1-8) was provided to the exercise leader prior to the study to guide them in performing each form of Tai Chi correctly.

### Interventions

#### Community-based multi-modal rehabilitation program group

Participants will receive 12 × 90 min sessions of supervised exercises over 12 weeks. In addition to usual care, supervised exercise will be held at the Center of Sports Training and Rehabilitation inside the University and each class will be restricted to no more than 8 participants to ensure sufficient personalized attention. Each training session involves warm-up together with stretching of lower extremity muscles (quadriceps femoris, hamstring, and calf muscle stretching) (10 min), strengthening exercises of the major lower extremity muscle groups by Theraband (isometric knee extensions in sitting/standing position, hip abduction, standing hamstring curls, and wall squat) (15 min), balancing exercise (side stepping, front crossover steps during forward/backward and laterally ambulation, back crossover steps during backward ambulation, shuttle walking, tandem walk, and standing on the foam surfaces) (15 min), Tai Chi training (20 min), and rest/ cool-down (15 min). All lower-extremity exercises will be performed bilaterally. The details of strengthening and balancing exercises are based on a previously published protocol [20], while the 12-form Sun style of Tai Chi is based on the “Tai Chi for Arthritis” program which involves six basic core movements and six advanced movements [12]. The 12 tai chi movements combine diaphragmatic breathing and relaxation with gentle and slow movements, both isometric and isotonic, while maintaining good postures. Tai chi exercise involves backward and forward movements with full-weight bearing on both lower extremities and qigong exercise with deep diaphragmatic breathing [12]. The written protocol with details of the intervention has been prepared and will be used by the exercise instructor.

Exercises are initially started at low intensity as indicated by the rate of perceived exertion (9–10 in the Borg scale 6–20) [21] and are progressively increased based on the overload principle [22], as long as participants do not experience significant increases in pain or discomfort (relative to the same day before the exercise class), increased effusion, or decreased range of knee motion following the exercises [23]. Intensity will be progressed based on individual ability, i.e., each participant will be monitored so that the difficulty of Tai Chi movements can be adjusted by varying the movement speed, magnitude of trunk rotation and weight shifting, base of support, and forward-backward movement with full weight-bearing on both lower extremities [12]. Each participant will be given both printed material and online videos about the Tai Chi exercises (including Tai Chi principles, practicing techniques, and safety precautions) (Additional file 2). Participants will be instructed to practice the same exercises at least 30 min daily to achieve 3 h of exercise per week [24]. The duration will be recorded in an exercise logbook, which will be checked every week to encourage adherence and to monitor the correct dosage. The logbook will be distributed to the participants at the beginning of the program and collected by the instructor at the last session. The Template for Intervention Description and Replication (TIDieR) Checklist has been adopted as a guideline for reporting the details of the intervention [25]. The fidelity of the intervention delivered by the instructor will be monitored and assessed by audio-recordings of sessions every 2 to 3 weeks. The principal researcher will listen to the voice clip and check whether the essential treatment components are included in each session using a checklist.

Upon completion of the supervised program, participants will be instructed to continue the exercises for 30 min per day at home until the postoperative 36-week follow-up (12-week home exercise). Previous research has recommended that fall prevention exercise should be no less than 50 h over 25 weeks to reduce fall risk in older people [24, 26]. The proposed exercise intensity will be 72 h over 24 weeks (12-week supervised exercise + 12-week home exercise). Further, the research personnel will contact participants by phone once every 2 weeks between the end of the 12-week program and the postoperative 36-week follow-up to facilitate their exercise adherence and document their weekly practice duration. Participants will be given supermarket coupons up to the value of HK$600 upon completion of all the 12-week intervention and 5 assessments.

#### Usual postoperative care group (Fig. 1)

Participants in the usual care arm will receive standardized usual inpatient postoperative care provided by the two participating hospitals and a total knee replacement pamphlet. The pamphlet contains information about early-stage postoperative exercises including lower limb stretching and mobilization exercises. In addition, some patients may be referred to outpatient physiotherapy services at the discretion of the physiotherapy or orthopedic team upon discharge or medical follow-ups. Upon the completion of all 5 assessments, participants will be given a maximum compensation of HK$250 supermarket coupons*.*

#### Untreated asymptomatic controls

To minimize the number of physical assessments for untreated asymptomatic controls, this group will undergo only three clinical assessments: at baseline and at 12 and 52 weeks after baseline (Fig. 1). Participants will be given a total possible compensation of $150 supermarket coupons only after the completion of 3 assessments.

## Endpoints and outcome measures

### Primary endpoint

The primary endpoint is to assess the feasibility and acceptability of trial design and procedures, including the recruitment and retention rates and identifying barriers to participation. This will inform the choice of the primary outcome for a full-scale trial and provide an estimation of the attrition rate for a sample-size calculation. The following will be measured and used to inform study feasibility:

#### Rate of recruitment and rate of retention

The recruitment rate will be calculated as the percentage of people who were screened for their eligibility for participating in the study and subsequently provided informed consent. The attrition rate will be calculated as the percentage of those recruited who did not complete reassessments at subsequent follow-ups. The recruitment and attrition rates will be monitored on a monthly basis to determine the presence of any specific trends. The recruitment rate (all potential participants), retention and attrition rates (all randomized participants), and completion rates (all enrolled participants) will be assessed at the end of study. Reasons for ineligibility and/or non-recruitment of eligible patients will be recorded and grouped into categories. Adverse events in all groups will be monitored, recorded, managed, and followed up. Participants will be given information regarding the procedure for reporting or handling of adverse events (e.g., a dedicated phone line for contacting the research team). All participants will have the right to withdraw from the study at any stage. The reasons for withdrawal will be documented and any data already collected from the participant will not be analyzed.

For participants who need to postpone their surgery after the baseline assessments, they will be reassessed 1 week before the rescheduled surgery. Participants who need to cancel their surgery after the baseline assessments will be treated as dropout cases and the corresponding reasons for non-participation will be documented. This procedure will enable the estimation of the recruitment rate and the sample size for the definitive trial.

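### The rule that data from withdrawn participants will not be analysed conflicts with the promised intention-to-treat analysis, and read literally it also removes their adherence and adverse-event data

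*Protocol article*

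**What the plan says.** Under 'Rate of recruitment and rate of retention' the protocol article states: "All participants will have the right to withdraw from the study at any stage". The next sentence sets the data rule: "The reasons for withdrawal will be documented and any data already collected from the participant will not be analyzed". It makes no exception for when the participant leaves, why, or what kind of data is concerned.

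Under 'Statistical analysis' the article states: "Following the intention-to-treat principle, between-group differences in primary and secondary continuous outcomes in all randomized participants at different time points will be analyzed". A narrower analysis is planned separately: "Per-protocol analysis will also be reported for all planned outcomes in participants who strictly followed the protocol". The same section plans the descriptive summaries: "The data regarding the feasibility, acceptability, adverse events, intervention adherence, missing data rates and data completion rates will be summarized using descriptive statistics". It names no separate population for adherence or safety.

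Two other statements limit the problem. On timing: "Upon completion of the 12-week post-operation assessments, TKA participants will be randomized into either the intervention or the usual care group". On the denominators of the feasibility rates: "retention and attrition rates (all randomized participants), and completion rates (all enrolled participants) will be assessed at the end of study".

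**The concern.** An intention-to-treat analysis keeps randomised participants in the comparison whether or not they continue. A rule that sets aside what a withdrawer has already provided undoes this and moves the main analysis towards the per-protocol analysis that is planned as its contrast. The analyst has two instructions that define different analysis sets, and nothing in the article says which prevails.

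The pilot exists to judge feasibility and acceptability and to supply figures for a definitive trial, including the SD of the KOOS. Attendance records and logbooks are its evidence on adherence. People who leave are likely to have attended less, and some may leave because of an adverse event. Leaving them out would make the programme look better attended and safer than it was.

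**Working it through.** **Is there a conflict?** The plan gives no figure to reproduce here, so the check starts with the two rules side by side.

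- Withdrawal before randomisation (before the week-12 assessment is complete): the participant is not in the randomised set, so there is no conflict with intention-to-treat.
- Withdrawal between weeks 12 and 24: the participant is randomised but has no post-randomisation assessment yet, because the first is at week 24. The rule discards the baseline, week-6 and week-12 assessments and, read literally, the attendance, logbook and adverse-event records.
- Withdrawal between weeks 24 and 52: the participant is randomised and has a week-24 outcome. The intention-to-treat sentence requires it to be analysed; the withdrawal rule forbids it. Outcome data are lost mainly here.

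**Adherence.** The 26 per arm comes from the Abstract. The article gives no withdrawal or attendance rates, so these are assumed: 5 of 26 withdraw after attending 30% of classes, and 21 attend 80%.

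- All randomised: (21 × 0.80 + 5 × 0.30) / 26 = (16.8 + 1.5) / 26 = 0.704, about 70%.
- Under the rule: 80%.

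With other assumed rates (completers 85%, withdrawers 30%), the figure for all participants is (1 − w) × 0.85 + w × 0.30. This gives 79.5%, 74% and 68.5% at withdrawal w = 10%, 20% and 30%, against 85% reported each time.

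**Adverse events.** Assume 10% of completers and 40% of withdrawers have an event. The rate in all participants is (1 − w) × 0.10 + w × 0.40, which gives 13%, 16% and 19% at w = 10%, 20% and 30%, against 10% reported.

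**Between-group effect at week 24.** Simulation with 26 per arm, a true difference of 0.50 SD and later withdrawal of 3 or 5 per arm (about 10% or 20%). In an arm with selective withdrawal, the leavers are those lowest on outcome plus noise of equal variance; otherwise they leave at random. Mean estimate after their data are discarded:

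| Selective withdrawal in | 3 of 26 | 5 of 26 |
|---|---|---|
| intervention arm only | 0.65 | 0.73 |
| both arms equally | 0.50 | 0.50 |
| usual care only | 0.35 | 0.27 |

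With a weaker link between outcome and withdrawal (noise SD 3), the first row becomes 0.57 and 0.60.

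**KOOS SD.** With equally selective withdrawal in both arms the difference is unbiased, but the analysed SD is about 0.92 (3 of 26) or 0.90 (5 of 26) of its true value. Sample size scales with SD squared: 0.92² = 0.85 and 0.90² = 0.81. A definitive trial planned on that SD would be about 15% to 19% too small. If withdrawal is unrelated to outcome, the SD is not biased.

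**The case against.** **Direction of the effect bias.** A reader might infer that the rule inflates the treatment benefit. The documents do not support that. They give no withdrawal rate and no information on who leaves from which arm, and the table shows that the estimate can be too high, too low or right.

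**Timing.** Participants who find the classes too hard would often leave during weeks 12 to 24, before any post-randomisation outcome exists. For them, keeping the data adds no outcome to the comparison. This stands, and it confines the loss of outcome data mainly to withdrawals between weeks 24 and 52. It does not touch the attendance, logbook and adverse-event data.

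**The pilot's main rates.** A reader might infer that retention and attrition are distorted too. They are not: their denominator is all randomised participants, and reasons for withdrawal are documented.

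**Safety.** The article says that adverse events in all groups are monitored, recorded and followed up, so the authors may not intend to drop withdrawers' events. That is fair; the loss follows from a literal reading and is not stated outright. But the rule covers any data, and no exception is made.

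**The repeated-measures model.** A reader might infer from "Separate two-way repeated measures analyses of covariate (ANCOVA) or ANOVA will be used" that everyone with a missed visit is dropped as well. The article does not say how missed visits are handled, which may be left to an analysis plan that is not shown. Missed visits are also a different matter from the withdrawal rule. With 5% to 10% assumed missing independently at each of the two post-randomisation visits, 0.95² = 90% to 0.90² = 81% would have both. This is no part of the finding.

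**Consent.** The rule may reflect an undertaking given to participants. The article does not show one. It speaks of withdrawing from the study and does not separate stopping the programme from asking that data not be used. A deletion request can be honoured without discarding every withdrawer's data.

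**Conclusion.** The inconsistency is real and should be corrected before the data are analysed. It is a stated rule that contradicts another stated rule, so an analysis plan that is not shown does not excuse it. For participants who withdraw after randomisation, the intention-to-treat set as written becomes a non-withdrawer set.

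The probable harm is to the adherence and adverse-event summaries: about 10 percentage points of adherence in the first example, on assumed rates. Its direction rests on withdrawers attending less, and having more adverse events, than those who stay. Bias in the between-group effect and the KOOS SD is possible, but neither its size nor, for the effect, its direction can be known from the documents. The range of 0.27 to 0.73 around a true 0.50 is an illustration, not a forecast.

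**What to change.** Replace the withdrawal sentence under 'Rate of recruitment and rate of retention' with: *All data collected up to withdrawal are kept and analysed in the intention-to-treat, adherence and adverse-event summaries, unless the participant explicitly asks for deletion; the number of such deletions is reported by arm.*

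As a supporting step, so that partial data can be used, analyse all available post-randomisation visits with a linear mixed model. The named software provides one. It will not supply an outcome for those who leave before week 24.

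The cost is a few sentences of wording, plus one check that matters: whether the consent already signed allows data to be retained after withdrawal. Recruitment was due to end on 1 November 2020, before the article appeared, so most participants have probably already consented. If the wording does not allow retention, the protocol should say so, stop describing the analysis as covering all randomised participants, and report by arm how many are excluded.
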